## Abstract

**Background:**

There is no consensus on which lung-protective strategies should be used in cardiac surgery patients. Sparse and small randomized clinical and animal trials suggest that maintaining mechanical ventilation during cardiopulmonary bypass is protective on the lungs. Unfortunately, such evidence is weak as it comes from surrogate and minor clinical endpoints mainly limited to elective coronary surgery. According to the available data in the academic literature, an unquestionable standardized strategy of lung protection during cardiopulmonary bypass cannot be recommended. The purpose of the CPBVENT study is to investigate the effectiveness of different strategies of mechanical ventilation during cardiopulmonary bypass on postoperative pulmonary function and complications.

**Methods/design:**

The CPBVENT study is a single-blind, multicenter, randomized controlled trial. We are going to enroll 870 patients undergoing elective cardiac surgery with planned use of cardiopulmonary bypass. Patients will be randomized into three groups: (1) no mechanical ventilation during cardiopulmonary bypass, (2) continuous positive airway pressure of 5 cmH_2_O during cardiopulmonary bypass, (3) respiratory rate of 5 acts/min with a tidal volume of 2–3 ml/Kg of ideal body weight and positive end-expiratory pressure of 3–5 cmH_2_O during cardiopulmonary bypass. The primary endpoint will be the incidence of a PaO_2_/FiO_2_ ratio <200 until the time of discharge from the intensive care unit. The secondary endpoints will be the incidence of postoperative pulmonary complications and 30-day mortality. Patients will be followed-up for 12 months after the date of randomization.

**Discussion:**

The CPBVENT trial will establish whether, and how, different ventilator strategies during cardiopulmonary bypass will have an impact on postoperative pulmonary complications and outcomes of patients undergoing cardiac surgery.

**Trial registration:**

ClinicalTrials.gov, ID: NCT02090205. Registered on 8 March 2014.

**Electronic supplementary material:**

The online version of this article (doi:10.1186/s13063-017-2008-2) contains supplementary material, which is available to authorized users.

## Background

Respiratory failure (RF) is a common complication in cardiac surgery, with a global incidence of 20–25%. Its clinical manifestation ranges from a mild form of respiratory failure up to an acute respiratory distress syndrome (ARDS) requiring prolonged mechanical ventilation (MV) and intensive care unit (ICU) stay [1].

The pathophysiological mechanism of RF is quite complex, but it is known that cardiopulmonary bypass (CPB) plays a major role in determining lung injury [2]. A number of factors contribute to this injury: atelectasis, hyperoxygenation causing the release of free radicals [3] and a CPB-related systemic inflammatory response [4, 5].

It is a common practice to suspend ventilation during CPB, since lung function is carried out by an extracorporeal gas exchanger. However, the interruption of MV during CPB is associated with the development of micro-atelectasis, hydrostatic pulmonary edema, reduced lung compliance and surfactant diffusion.

A recent observational study [5] has identified the duration of CPB as an important risk factor for the development of microbiologically documented pneumonia.

Over recent years, several preventive lung-protective strategies have been investigated and proposed [6, 7]: ultrafiltration to remove neutrophils [8], controlled hemodilution (with a hematocrit higher than 23%), steroids [9] and adjusting MV settings during CPB, such as the application of positive end-expiratory pressure (PEEP) or continuous positive airway pressure (CPAP) of 5–15 cmH_2_O, low tidal-high frequency ventilation (100 acts/min), the application of 100% oxygen inspired fraction (FiO_2_), and bilateral CPB which involves using the lungs for blood oxygenation [10].

A recent meta-analysis [11] based on 16 clinical trials found an increase in oxygenation and a reduction in shunt fraction [11, 12] immediately after weaning from CPB if CPAP was applied during CPB. Similar results were obtained with a lung recruitment maneuver (RM) [13] at the end of CPB. Furthermore, maintaining MV during the entire duration of extracorporeal circulation would reduce the CPB-related inflammatory response and resultant tissue damage [14–16]. Unfortunately, although adequately planned, studies are not powered enough to recommend maintaining MV during CPB as an evidence-based strategy to prevent respiratory complications because major indicators of clinical outcome (i.e., duration of postoperative MV, length of ICU and hospital stay, and long-term follow-up) have not been investigated [17–19]. Therefore, according to the available data in the academic literature, an unquestionable standardized strategy of lung protection during CPB cannot be recommended [20–24].

### Objectives

We designed a randomized controlled trial to investigate the effects of three different ventilator strategies in the short, medium and long term. We are testing the hypothesis that MV during CPB would reduce the incidence of RF, defined as an arterial oxygen tension (PaO_2_) and inspiratory oxygen fraction (FiO_2_) ratio (PaO_2_/FiO_2_) <200, and other postoperative pulmonary complications (PPCs).

We identified the PaO_2_/FiO_2_ ratio as a summarizing parameter, even if it is still imprecise and unspecific, because many different conditions leading to respiratory insufficiency and hypoxemia can be assessed as a PaO_2_/FiO_2_ ratio modification. We chose it because we were looking for an objective value that can be easily calculated by any trained health care operator and that is not affected by the physician’s judgment. A decreased lung compliance, increased alveolo-arterial oxygen difference and increased intrapulmonary shunt fraction may all lead to a decreased (PaO_2_/FiO_2_) ratio. [25, 26]

## Methods/design

### Trial design

The CPBVENT study is a nonpharmacological, multicenter, single-blind, randomized controlled trial. Protocol structure was written in compliance to the Consolidated Standards of Reporting Trials (CONSORT) 2010 Statement guidelines and follows the Standard Protocol Items: Recommendations for Interventional Trials (SPIRIT) Statement). The SPIRIT checklist of this trial can be found in Additional file 1. The SPIRIT figure of this trial is illustrated in Fig. 1.

**Fig. 1 Fig1:**
[figure not shown]
The SPIRIT figure of this trial

The study has been registered at ClinicalTrials.gov with the registration number NCT02090205 and was endorsed by the Study Group on Cardiothoracic and Vascular Anesthesia of the Italian Society of Anesthesia and Intensive Care Medicine (SIAARTI).

### Participants

After Ethics Committee approval, on 2 October 2014 (Approval number 69/INT/2014), we intend to enroll patients aged 18 years or over who are undergoing elective cardiac surgery with planned use of CPB, aortic cross-clamping, median sternotomy and two-lung ventilation. All patients will provide written informed consent before their inclusion in the trial. The inclusion and exclusion criteria are shown in Table 1 (LAS VEGAS study: NCT01601223, [27]).

**Table 1 Tab1:** Inclusion/exclusion criteria

Eligibility criteria	
Inclusion criteria • Age ≥18 years • Ability to provide informed consent • Elective cardiac surgery • Surgical intervention performed with CPB, aortic cross-clamping and cardioplegic arrest • Valvular surgery, coronary surgery, surgery on the ascending aorta, combined cardiac surgery • Median sternotomy and bi-pulmonary ventilation	Exclusion criteria • Patient’s refusal • Nonelective cardiac surgery • Previous cardiac surgery • Anticipated circulatory arrest, aortic endoprothesis, TAVI, Mitraclip • Thoracotomic approach, with one lung ventilation • Patients with BMI >30 [24] • Patients with end-stage chronic kidney disease (defined as need for dialysis) • Patients with known respiratory diseases (ongoing respiratory infections, asthma, COPD, OSAS) • Patients already intubated before arrival in operating theatre • Pneumonia in the previous 30 days • Previous pulmonary resection • Patients with a preoperative oxygen saturation <90%, or P_a_O_2_ < 60 mmHg without supplemental oxygen, or a PaO_2_/FiO_2_ ratio <300, or P_a_CO_2_ > 45 mmHg • Patients with hepatic disease, defined as elevated liver enzymes (higher than two reference intervals) • Patients with pulmonary hypertension (defined as preoperative estimated systolic pulmonary artery pressure >45 mmHg)

*BMI* Body Mass Index, *CPB* cardiopulmonary bypass, *COPD* chronic obstructive pulmonary disease, *FEV*
_*1*_ forced expiratory volume in 1 s, *FiO*
_*2*_ fraction of inspired oxygen, *HF* high-frequency, *OSAS* obstructive sleep apnea syndrome, *PaCO*
_*2*_ arterial partial carbon dioxide pressure, *PaO*
_*2*_ arterial partial oxygen pressure, *TAVI* transcatheter aortic valve implantation

### Endpoints

The primary endpoint will be the incidence reduction of PaO_2_/FiO_2_ ratio <200 until discharge from the ICU [28, 29].

The secondary endpoints will be the evaluation of the following:Readmission to the ICU for RFThe global incidence of PPCs after cardiac surgery (see Table 2 for complete definition)

**Table 2 Tab2:** Definition of postoperative pulmonary complications (PPCs)

Complication	Definition
Respiratory insufficiency	At least one of the following criteria: • SpO_2_ < 90% • PaO_2_/FiO_2_ < 300 • PaCO_2_ > 45 mmHg • Dyspnea with respiratory distress or use of accessory muscles
Respiratory infection	Evidence of new pulmonary infiltrates on chest radiograph plus at least two of the following Johanson criteria: • Body temperature >38 °C or <35.5 °C • White blood cell count >12,000 mm^3^ or <4000 mm^3^ • Purulent sputum • Presence of a new or evolving infiltrate on chest radiograph within 7 days after surgery
Pleural effusion	Evidence of new hazy opacity of one hemithorax with preserved vascular shadows on the supine radiograph, or posterior costophrenic angle blunting on a lateral chest radiograph, or evidence of a new hypo-anechoic area between visceral and parietal pleura on chest ultrasonography
Atelectasis	Evidence on chest radiography of new parenchymal thickening surrounded by hyperinflated lung
Aspiration pneumonitis	Inhalation of gastric content in the perioperative period with subsequent acute lung injury
Bronchospasm	New expiratory wheezing responsive to treatment with bronchodilators
Pneumothorax	Presence of air within the pleural space detected with chest radiograph or loss of lung sliding of gliding sign on ultrasonographic lung examination

*PaO2* arterial partial oxygen pressure, *PaCO2* arterial partial carbon dioxide pressure, *SpO*
_*2*_ oxygen saturationNeed for re-intubationNeed for noninvasive ventilationDuration of mechanical ventilationLength of the ICU and hospital stayCardiovascular complicationsShort-term and long-term mortalityPostoperative infectionsPostoperative residual curarization (PORC): measured with a Train of Four (TOF) and defined as a “need for pharmacological reversal”

### Interventions (randomization and treatment protocol)

The randomization list was created by the coordinating center with a dedicated software and stratified per center, in a 1:1:1 ratio, in blocks of 30. Once the patient has provided informed consent, the investigator logs into a dedicated on-line portal to obtain the allocation arm. From that moment it will be impossible to remove the patient’s record card from the online platform and, in any case, the patient will be analyzed according to the intention-to-treat principle. Any deviation from the ventilation protocol, together with reason for deviation, will be recorded on the Case Report Form (CRF). All patients will be kept blind to the allocation.

Patients will be randomly assigned to receive one of the following ventilator strategies [20] (Fig. 2):

**Fig. 2 Fig2:**
[figure not shown]
Ventilation flowchart. Description of the ventilatory strategies used before, during and after cardiopulmonary bypass. Abbreviations: *CPB* cardiopulmonary bypass, *VC-CMV* volume-controlled continuous mandatory ventilation, *TV* tidal volume, *IBW* ideal body weight, *PEEP* positive end-expiratory pressure, *FiO*
_*2*_ inspired oxygen fraction

*First arm*. No mechanical ventilation during CPB: patient will be disconnected from the respiratory circuit
*Second arm*. Patients will receive CPAP with PEEP of 5 mmH_2_O and FiO_2_ < 80%. To perform CPAP the ventilator will be set in manual/spontaneous mode, with a flow of 1–2 L/min and the adjustable pressure valve (APL) set at 5 cmH_2_O. The actual pressure will be checked with a pressure gauge integrated in the ventilator and a pressure gauge connected to the proximal end of the endotracheal tube
*Third arm*. Patients will be ventilated with a respiratory rate of 5 acts/min, with tidal volume (TV) of 2–3 mL/Kg of ideal body weight (IBW) and PEEP of 3–5 cmH_2_O

Before and after CPB patients will receive a lung-protective ventilator strategy [23, 30–32], with a volume-controlled continuous mandatory ventilation (VC-CMV) mode along with the following parameters [20] (Fig. 2):Tidal volume (TV) = 6–8 ml/Kg of IBW [22]PEEP = 5 cmH_2_OFiO_2_ < 80%I:E = 1:2 (inspiration:expiration ratio)

During CPB our goal will be to maintain PaO_2_ between 200 and 250 mmHg in order to avoid hyperoxia-induced lung injury [3, 33]; moreover, the hematocrit will be maintained above 24% [34]. During weaning from CPB we will perform a single alveolar RM. This RM will be performed manually by the anesthesiologist with a gas mixture of oxygen and air (with an inspired oxygen fraction lower than 80%), keeping an airway pressure of 40 cmH_2_O for at least 7 s [35]. RM duration and any additional RM in ICU will be recorded. Immediately after the end of RM, ventilation with PEEP will be resumed. If any additional RM is be performed in the ICU, this will be done with the same procedure as in the operating room.

A FiO_2_ lower than 80% will be set during all perioperative time, since a higher oxygen fraction is widely recognized as harmful [3, 21, 36]. The oxidative stress caused by hyperoxia could itself be a source of lung damage.

### Postoperative ventilation

The anesthesiologist will report in the CRF the mechanical ventilation setting used during patient transfer from the operating theatre to the ICU. In the ICU we will apply a VC-CMV with the same parameters used in the operating room. Blood oxygen saturation will be constantly monitored with a pulse oximeter. We will report the extubation time, the duration of mechanical ventilation and the need for re-intubation. Blood gas analyses will be performed by the clinician according to clinical needs.

### Perioperative management and monitoring

All participating patients, regardless of the study arm into which they are randomized, will be monitored and managed following general standard of care practices which aim at maintaining optimal conditions. Both intraoperative and immediate postoperative anesthetic management (unrelated to ventilatory management) will be decided by the attending physician as they see fit, following the established protocols at each center. Any decision affecting the protocol will be recorded on the electronic CRF (eCRF).

Intraoperative monitoring will include an electrocardiogram (ECG), pulse oximeter, capnography, urine output, invasive blood pressure measurements, advanced hemodynamic monitoring (pulmonary artery catheter (PAC)/transesophageal echocardiogram (TEE)), bladder or esophageal temperature, and Activated Clotting Time (ACT). Monitoring of anesthetic depth analysis (bispectral analysis, BIS) and neuromuscular blockade (with TOF) are optional depending on the standard clinical practice and availability of equipment at each hospital.

The anticoagulant protocol is as follows: heparin (3 mg/Kg) to achieve an ACT of 200 s for cannulation and 480 s to proceed with the CPB. At the end of the CPB, protamine (3 mg/Kg) is used (ACT target <150). In case of allergy to heparin, we will administer bivalirudin.

During CPB, mild hypothermia (31–33 °C) and pump flow of 2.5 L/min/m^2^ will be applied.

Ventilatory parameters will be monitored by the anesthesia machine: TV, PEEP, FiO_2_, peak airway pressure (Paw) and plateau pressure (Pplat).

### Data collection and follow-up variables

Investigators will collect all the data on the dedicated CRF and will insert all the information required in the online platform. The coordinating center will directly receive all the information in a very simple data flow, with safe mechanisms for the protection of personal clinical information. The website uses an https format and all patients’ data will be collected anonymously. We have also implemented regular backups in order to minimize the risk of data corruption. Only the principal investigator and the data managers of the coordinating center will have access to the main database.

Data collection will include: preoperative information (anamnesis, physical examination, cardiac and pulmonary function, laboratory analysis), intraoperative data (ventilatory parameters, type of anesthesia, type of cardioplegia, type of CPB circuit, temperature during CPB, use of volatile anesthetics in CPB, volume and type of fluids administered, transfusion requirements, use of vasoactive drugs, duration of intervention, ventilation mode used during transport to the ICU), postoperative data (use of inotropic or vasoactive drugs, mechanical devices, time to extubation, need for respiratory support or re-intubation and hospital stay). Furthermore, we will calculate the Euroscore I–II, the ACEF score [37] and the ARISCAT risk score [38].

After discharge from the hospital, patients will be phoned for the follow-up. We will record any re-admission to hospital or exitus. Follow-up will be performed 30 days, 60 days and 1 year after randomization; we will consider overall mortality.

### Statistical considerations

#### Sample size

Sample-size calculation was based on a two-sided alpha error of 0.05 and a 80% power (beta). On the basis of respiratory insufficiency incidence after cardiac surgery, we anticipate that 25% of patients will have a PaO_2_/FiO_2_ ratio <200. We expect a reduction of 35% in the incidence of this parameter. We calculate that we will need a sample size of 263 patients per group, 789 in total. Including a dropout fraction of 10%, we calculate that we will need 870 patients to complete the trial.

A significant blind interim analysis (*P* < 0.0001) will be performed once half of the patients have been recruited to assess the recruiting progress and verify that the hypotheses assumed in the calculation of the sample size are correct.

#### Data analysis

We will analyze patients in the treatment group to which they are allocated. Data will be analyzed with professional statistical software. Data will be analyzed according to the intention-to-treat principle and following a pre-established analysis plan. Dichotomous variables will be compared with the two-tailed *Χ*
^2^ test, using the Yates correction when appropriate. Continuous variables will be compared by analysis of variance or the nonparametric Kruskal-Wallis test, when appropriate. Relative risks with 95% confidence intervals, and differences between medians with 95% confidence intervals (using the Hodges-Lehmann estimation), will be calculated when appropriate. Two-sided significance tests will be used.

The major comparison will be between the two groups undergoing MV during CPB and the group with no MV.

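### Randomisation is stratified by centre, but the test named for the primary endpoint ignores centre and leaves the Yates correction open: a modest efficiency loss, not a validity error

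*Protocol article*

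**What the plan says.** The section on interventions and randomisation describes an allocation list "stratified per center, in a 1:1:1 ratio, in blocks of 30". Current trial status plans for at least 20 centres.

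The Data analysis section says "Dichotomous variables will be compared with the two-tailed" chi-square "test, using the Yates correction when appropriate". The primary endpoint, any PaO2/FiO2 ratio below 200 before ICU discharge, is a binary variable, so this sentence covers it. Relative risks with 95% intervals are also promised. No stratification or adjustment by centre is named anywhere in the article. The major comparison sets the two groups ventilated during bypass against the unventilated group. The section also refers to a pre-established analysis plan, which is not shown.

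Two passages bear on whether centres will differ. Under Postoperative ventilation, blood gas sampling is left to the clinician's view of need. Under Perioperative management and monitoring, anaesthetic care other than ventilation "will be decided by the attending physician as they see fit, following the established protocols at each center".

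**The concern.** A factor used to stratify randomisation should normally be carried into the analysis. Stratification balances the arms within centres, which reduces the true sampling variation of the treatment difference when centres differ in event rate. An unstratified chi-square does not take credit for that balance: its variance still contains the between-centre component, so the test rejects less often than its nominal level.

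Centre differences are plausible here. The endpoint is detected only when a blood gas is drawn, and drawing one is a local decision. Ventilator settings are standardised across centres, so the sampling habit is a stronger reason than the freedom in anaesthetic care.

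The Yates correction pushes in the same direction. Because its use has no stated criterion, the primary P value could be either of two numbers. What is at stake is some power, and one analysis decision left open.

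**Working it through.** **Inputs from the Sample size section.** Two-sided alpha 0.05 and power 80%; "we anticipate that 25% of patients will have a PaO_2_/FiO_2_ ratio <200"; "We expect a reduction of 35% in the incidence of this parameter"; "263 patients per group, 789 in total". The reduction must be relative, since a 35-point fall from 25% is impossible. The target rate is 0.25 × 0.65 = 0.1625.

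**Step 1: reproduce the plan's figure.** Take the pooled comparison, allocation ratio r = 2, difference d = 0.0875, and average rate p = (0.25 + 2 × 0.1625)/3 = 0.1917.

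- Uncorrected control-group size: n = [1.960 √((r+1)p(1−p)) + 0.842 √(r × 0.25 × 0.75 + 0.1625 × 0.8375)]² / (r d²) = (1.3362 + 0.6017)² / 0.015313 = 245.3, so 246.
- Continuity-corrected: (n/4)[1 + √(1 + 2(r+1)/(n r d))]² = 61.31 × (1 + √1.1398)² = 262.1, so 263.

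With 526 ventilated patients this gives 789, an exact match. The trial therefore appears to have been sized for a corrected 2:1 test.

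**Step 2: cost of Yates with no centre effect.** Exact enumeration at 263 v 526:

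- Power is 82.8% for plain chi-square and 80.4% with Yates.
- Type I error at a 25% rate is 5.0% and 4.1%.
- The smallest expected cell is 263 × 0.1917 = 50, so the correction is not needed.

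**Step 3: cost of ignoring centre.** We simulated 789 patients in 20 centres of uneven size, in blocks of 30, with 20,000 runs per setting, comparing the two ventilated groups with control. Number and sizes of centres and the between-centre SD (logit scale) are assumptions. Each triplet is plain chi-square / Yates / centre-stratified Cochran-Mantel-Haenszel.

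| SD | 10th–90th centile of centre control rates | Type I error, % | Power, % | Stratified minus plain, points | Stratified minus Yates, points |
|---|---|---|---|---|---|
| 0 | 25–25% | 4.9 / 3.9 / 4.9 | 82.4 / 79.8 / 81.9 | −0.5 | +2.1 |
| 0.3 | 18–32% | 4.9 / 3.8 / 4.9 | 82.4 / 80.0 / 82.3 | −0.1 | +2.4 |
| 0.5 | 14–37% | 4.8 / 3.9 / 5.2 | 82.7 / 80.2 / 83.4 | +0.8 | +3.3 |
| 0.75 | 10–43% | 4.0 / 3.3 / 4.8 | 83.5 / 80.9 / 84.8 | +1.4 | +4.0 |
| 1.0 | 7–49% | 4.1 / 3.2 / 5.3 | 83.8 / 81.2 / 86.4 | +2.6 | +5.2 |

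Differences are taken before rounding. Monte Carlo standard error is about √(0.05 × 0.95/20,000) = 0.15 points for type I error and √(0.82 × 0.18/20,000) = 0.27 points for power.

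**Step 4: the relative-risk interval.** Under the null, the mean unadjusted standard error of the log relative risk divided by its true standard deviation is 0.1315/0.1317 = 1.00 at SD 0, 0.1324/0.1316 = 1.006 at SD 0.5, 0.1335/0.1300 = 1.027 at SD 0.75 and 0.1347/0.1303 = 1.034 at SD 1.0. Under the planned effect the unadjusted interval covers about 95% throughout. The Mantel-Haenszel interval covers 94.8% at SD 0.5 and 93.5% at SD 1.0. The case for stratifying therefore rests on the test, not on the interval.

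**The case against.** **The analysis plan may already stratify.** It is not shown, and a journal article may leave such detail to it. Silence about centre alone would not be a finding. What remains is that the article does name a test, and that test does not use the design. If the analysis plan stratifies, the two texts disagree and should be aligned.

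**The centre effect is assumed.** This stands. If centres are alike the loss is nil, and at SD 0.5 it is under one point of power against plain chi-square. Gains near five points need both extreme centre variation and use of Yates.

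**Yates may not be used, and seems paid for.** This also stands in part. The wording does not require Yates for the primary comparison, and 263 per group matches the corrected formula. The open choice remains.

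**Stronger readings.** A reader might infer that true type I error lies well below 5%, that the confidence intervals are materially too wide, or that the choice of test leaves the trial underpowered. The documents support none of these. Plain chi-square stays at 4% or above in every setting run. The interval is affected by a few per cent at most, and not at all by Yates, which alters only the test. The article's own warning of an underpowered result concerns its assumed 25% incidence, not its test.

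**Conclusion.** The point holds as one of efficiency and clarity. The named test is valid and errs on the cautious side. Across the assumed range, stratifying by centre restores type I error to about 5%. Power changes by about −0.5 to +2.6 points against plain chi-square and by about +2 to +5 points against Yates.

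The stated 80% is met for the pooled 2:1 comparison: 80.4% exactly with Yates, and 79.8 to 81.2% in the simulations. That statement depends on the pooled reading. For one ventilated arm against control (263 v 263), simulated power without centre differences is 70.1% plain, 66.2% with Yates and 69.5% stratified. That shortfall comes from the size of the comparison, not from leaving out centre.

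The size of the gain rests on a between-centre variation that the article does not give. Adjustment for further baseline covariates is optional and forms no part of this point.

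**What to change.** State that the primary analysis is a centre-stratified Mantel-Haenszel test with the corresponding relative risk and 95% interval. Fix in advance a rule for pooling very small centres. State that Yates is not applied to the primary comparison. Keep the unstratified chi-square as a sensitivity analysis. If the unseen analysis plan already says this, align the article's wording with it.

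The change needs wording only, because centre is known for every patient from the stratified allocation. Recruitment was still open at the date given in the article (559 of 870 patients), so the wording should be settled before outcomes are compared by arm. The statistical price is about half a point of power if centres turn out not to differ.

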Furthermore, we acknowledge that the incidence of 25% for a PaO_2_/FiO_2_ ratio <200 is high and, even if it is the one we experienced in our daily practice, the risk of a final underpowered result is still present. Our choice was driven by our clinical experience but also by feasibility. On the other hand, this study is still the largest ever performed on this topic and we hope to provide some important insights into CPB-related lung injury pathophysiology and prevention.

Pulmonary artery perfusion during CPB [63] and pulsatile pulmonary perfusion [64] have been proposed as a further approach to attenuate the CPB-related lung dysfunction. Still, the currently available techniques of pulmonary perfusion during CPB are still emerging and their feasibility is strongly linked to the surgeon’s experience.

Finally, we are aware that the results obtained from a specific subgroup of patients, with strict inclusion criteria, may not be generalizable to the whole population. However, since this is the first large trial ever performed on this topic, we decided to create a clean experimental setting. Further research will be necessary to assess whether our findings are extendible to other subgroups and to the general population of patients undergoing to cardiac surgery with CPB.

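### The article fixes an unadjusted test for the primary endpoint although patient risk scores are calculated: a modest, nearly free efficiency gain is missed, but the test is valid

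*Protocol article*

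**What the plan says.** **Test.** Protocol article, Data analysis: "Dichotomous variables will be compared with the two-tailed" chi-square test, Yates-corrected where suitable, with relative risks and 95% confidence intervals. The primary endpoint is dichotomous, so this is its stated analysis. No covariate is named. The same section names the two ventilated groups against the unventilated group as the main comparison and refers to a pre-established analysis plan, which is not shown.

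**Risk information.** Data collection and follow-up variables: "we will calculate the Euroscore I–II, the ACEF score [37] and the ARISCAT risk score [38"]. No later section mentions these scores. Table 1 admits coronary, valve, ascending-aorta and combined operations. Allocation is equal across three arms and stratified by centre only.

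**Planning figures.** Sample size: "a two-sided alpha error of 0.05 and a 80% power (beta"); "we anticipate that 25% of patients will have a PaO_2_/FiO_2_ ratio <200"; "We expect a reduction of 35% in the incidence of this parameter"; "we will need a sample size of 263 patients per group, 789 in total".

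**Power caveat.** Limitations: "the risk of a final underpowered result is still present". The article ties this to the 25% rate being high.

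**The concern.** When a baseline variable predicts a binary outcome, an unadjusted comparison leaves explainable variation in the error. Adjusting for that variable gives more power from the same patients. It also takes account of a chance difference between arms in risk or type of operation. Here the scores are calculated anyway, so the extra information costs almost nothing. The article is not silent on method: it publishes an unadjusted test. If an adjusted model is wanted, it has to be chosen before results are seen by arm, because covariates picked afterwards carry little credibility. At stake are a few points of power on the main comparison.

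**Working it through.** **Inputs from the Sample size section.** Two-sided alpha 0.05 (z = 1.960); power 80% (z = 0.842); p1 = 0.25; p2 = 0.25 × 0.65 = 0.1625; difference d = 0.0875; 263 per group, 789 in total. Pooling the two ventilated arms gives 263 against 526, ratio k = 2.

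**Reproducing the plan's figure.** Mean rate = (0.25 + 2 × 0.1625)/3 = 0.1917, so p̄q̄ = 0.1549.

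n = [1.960 √(1.5 × 0.1549) + 0.842 √(0.1875 + 0.1361/2)]² / 0.0875² = (0.945 + 0.425)² / 0.007656 = 245.3, that is 246.

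With continuity correction: (246/4) × [1 + √(1 + 2 × 3/(246 × 2 × 0.0875))]² = 61.5 × 4.274 = 262.9, that is **263**. The stated 263 per group (789) is matched exactly by the pooled 2:1 comparison with continuity correction. The design and the named test therefore agree at 80%.

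**Unadjusted power without the correction.** z = (0.0875 √263 − 0.945)/0.5055 = 0.938, so power is **82.6%**.

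**Power with one score adjusted for.** Assumption: the article does not say how well any score predicts PaO2/FiO2 below 200, so a range of AUC is shown. R² is the share of outcome variance that the score explains at an average event rate of 20%. The formula above is used with n replaced by 263/(1 − R²). At R² = 0.082, for example, 263/0.918 = 286.5 and z = (0.0875 √286.5 − 0.945)/0.5055 = 1.06, giving 85.5%. The last two columns come from 6,000 simulated trials per row, with a logistic outcome, one normally distributed score and the marginal rates held at 25% and 16.25%.

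| Assumed AUC | R² | Analytic power | Gain over 82.6% | Simulated crude | Simulated adjusted |
|---|---|---|---|---|---|
| 0.50 (no prediction) | 0 | 82.6% | 0 | 82.4% | 82.2% |
| 0.60 | 0.020 | 83.3% | 0.7 | 83.1% | 83.9% |
| 0.65 | 0.046 | 84.3% | 1.7 | 81.8% | 83.2% |
| 0.70 | 0.082 | 85.5% | 2.9 | 82.3% | 85.0% |
| 0.75 | 0.134 | 87.4% | 4.8 | 82.2% | 86.5% |
| 0.80 | 0.201 | 89.8% | 7.2 | 83.0% | 89.4% |

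The simulation error is about √(0.83 × 0.17/6,000) = 0.5 points, and the two methods agree to within about 1 point. A separate simulation of 4,000 trials per setting gave 83.0% crude to 84.3% adjusted at AUC 0.64, 82.4% to 85.9% at 0.71, and 82.4% to 88.0% at 0.76. The Yates-corrected crude test had 79.9-80.7% in those runs. The gap between Yates-corrected and uncorrected power comes from the correction and is not credited to adjustment here.

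**If the control rate is lower.** Same 35% reduction, 263 against 526:

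| Control rate | Crude | R² 0.05 | R² 0.08 | R² 0.13 |
|---|---|---|---|---|
| 20% | 71.9% | 74.0% | 75.3% | 77.5% |
| 15% | 58.2% | 60.3% | 61.6% | 63.9% |

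Adjustment recovers about 2 to 6 points and stays below 80% in every cell.

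**The case against.** The strongest reply is that nothing here is wrong. An unadjusted chi-square test in a randomised trial controls type I error, which already allows for chance imbalance, and it delivers the power that was planned. The article also cites an analysis plan that is not shown, and choice of covariates is often left to such a plan. Both points stand, and they limit this to an improvement. They do not remove it, because the article does state a method, and a plan with an adjusted primary model would depart from the published text.

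Four stronger readings that a reader might infer are not supported:

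- *That the trial never uses the scores.* This can be said only of the article. The plan is not shown, and the Subgroup analyses section names no subgroups, so the scores might define some.
- *That randomisation leaves risk or operation type unbalanced.* It balances them in expectation; stratifying on them would only tighten this.
- *That the admitted risk of low power supports the point.* That admission concerns the 25% control rate, and the last table shows that adjustment does not make up such a shortfall.
- *That a large gain is likely.* Table 1 excludes known respiratory disease, BMI above 30, poor oxygenation and pulmonary hypertension, and Limitations describes a low-risk, homogeneous group. A narrow risk range favours the weak end of the table.

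It is also fair to object that the simulation used one complete covariate in a correctly specified model. Power for the exact analysis proposed below was not computed.

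**Conclusion.** The point holds as a missed efficiency gain. The stated primary test is valid and reaches 80% with its continuity correction (82.6% without). One score with AUC 0.60-0.70 would bring power to about 83-86%, and one with AUC 0.75-0.80 to about 87-90%. Given the restricted eligibility, a gain of about 1 to 3 points is the more plausible size. The figures rest on pooling the two ventilated arms, on 263 against 526 analysed patients, on the planned rates, and on an assumed prognostic strength for which the article gives no figure. If each ventilated arm were compared separately with control (263 against 263), crude power would be 70.0%, rising to 70.8-79.4% over the same AUC range.

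**What to change.** Before any unblinded look, pre-specify as the primary analysis a logistic model of PaO2/FiO2 below 200 on treatment plus a short fixed set of baseline covariates, for example one cardiac risk score and planned operation type. Use only items known before surgery; the article does not say when the scores are fixed or which items enter them. One score is enough, since several would overlap. Report the standardised (marginal) relative risk with its 95% confidence interval, and keep the crude chi-square test as supportive. If the existing analysis plan already specifies this, say so and align the article's wording with it.

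The cost is an amendment to the analysis wording during the trial and a rule for missing covariates. Planned operation type is not named in the list of collected data, so its place on the CRF should be confirmed. The article reports 559 of 870 patients recruited, beyond the half-way point (435) set for the interim analysis. That analysis is described as blind; the amendment should record that no results by arm had been seen when the covariates were chosen.
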